## Trial status

Recruitment of patients began in January 2020 with protocol version 4.3.2. HC entered the trial at the end of June 2021 following postponing due to the COVID-19 pandemic. Recruitment of both patients and HC is still open and will approximately be completed end of June 2022.

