### Objectives {7}

The main objective of this trial is to longitudinally investigate the influence of 6 months PUFA administration on the gut microbiome composition of adolescent patients with AN over the course of hospital treatment and at 1 year follow-up compared to a placebo arm and in comparison to longitudinal changes in gut microbiome composition in healthy adolescents. Primary clinically relevant outcomes will be microbiome composition changes and weight gain. We furthermore want to study the effect of PUFA supplementation on eating disorder psychopathology, comorbidities, and gastrointestinal symptoms. To further deepen our understanding of the underlying pathophysiologic mechanisms, we want to elucidate the influence and interaction of the microbiota with the brain (microbiome-gut-brain axis) by conducting structural and functional Magnetic Resonance Imagining measurements as well as neuropsychological tests in our patients and in a group of HC. In addition, the interaction of the microbiome and inflammation markers, gut permeability, and hormones is investigated to study their role for the potential anti-inflammatory effect of PUFA in AN. Our hypotheses are that PUFA will have an anti-inflammatory effect mediated by the microbiota. Microbiome changes will furthermore lead to a reduction of the “leaky gut” and ameliorate energy utilization of the food consumed. Together, we expect these underlying mechanisms to lead to an increase in weight and a reduction in eating disorder and comorbid psychopathology as well as gastrointestinal symptoms, compared to the placebo group. Comparison to HC will further facilitate the understanding of the basic pathomechanisms of microbiome-gut-brain interaction in AN and help estimate the extent of normalization achieved by our intervention.

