### Trial design {8}

The MiGBAN study is a longitudinal, double-blind, randomized, placebo-controlled superiority clinical trial with an observational HC group. Sixty AN patients will systematically be assessed directly after admission (measurement time point TA; pre-interventional baseline measurement), at discharge (TD), after 6 months (T6; post-intervention) and after 12 months (T12). Randomization to either PUFA or placebo will be performed as a stratified block randomization with a 1:1 allocation ratio. Stratification factors are sex, typical/atypical AN and MRI/non-MRI participation. For the 30 HC, only the measurement time points TA and T6 apply, and these participants will not receive any intervention (see Fig. 1 for an overview of the planned trial design). The trial was approved by the local Research Ethics Committee at the University Hospital RWTH Aachen (reference EK 194/19) and will be carried out in accordance with the Declaration of Helsinki. The study was registered at the German Clinical Trials Register (DRKS00017130, 12 November 2019).

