### Sample size {14}

So far, only one small study investigated the effects of providing PUFA compared to saturated fatty acids in patients with AN and found an effect size in weight gain of *d* = 1.0 [24]. Meta-analyses of probiotic interventions in depression and anxiety disorders revealed a pooled effect size of *d* = 0.68 for improvements in depressive symptoms and *d* = 0.66 for improvements in anxiety symptoms compared to placebo [38]. Thus, for the present study, we assumed an effect size of *d* = 0.8 for the effect of PUFA compared to placebo on BMI. To detect this effect using a two-sided *t*-test with a power of 80% at a significance level of *α* = 0.05, a sample size of 26 patients per group is needed. Considering a rate of loss-to-follow-up until 12 months of 10–15%, 30 patients per group, respectively 60 patients in total will be included in the trial. In case the final analysis will include 30 patients per group, the expected power (assuming an effect size of *d* = 0.8) will be 86%. For effect sizes of *d* = 1.0 and *d* = 0.65 as reported by previous studies mentioned above, the power will be 97% and 70%, respectively. No previous studies providing effect sizes for microbiome composition are available, but the direct effect of PUFA on microbiome composition can be expected to be at least as strong as the indirect effect on BMI.

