### Recruitment {15}

Patient recruitment will take place in the Aachen Eating Disorder Unit. Every patient aged between 12 and 19 years admitted with a diagnosis of AN or atypical AN according to DSM-5 and his or her parents or caregivers will be provided detailed information about the study. Coupons for cinema visits and local stores are offered as remunerations for all as well as additional travel cost refunds for follow-up visits. The Aachen Eating Disorder Unit admits on average 50 patients with AN per year out of which 60 will be recruited in 2 years’ time (according to our previous study ANDI, in which two thirds of the eligible patients agreed to participate; [39]). Drop out until 12-month follow-up is estimated at no more than 10% according to previous clinical trials at our institution (6%, [39]; 4.5%, [40]). Age- and sex-matched HC will be recruited via advertisements and flyers in schools in Aachen and from participant lists of previous studies conducted at the Department of Child and Adolescent Psychiatry, Psychosomatics and Psychotherapy, University Hospital RWTH Aachen.

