Finally, in addition to the randomized comparison between PUFA and placebo groups, a comparison between HC and patients (in both arms) will be done to assess both differences in gut microbiome composition and diversity between patients with AN and HC in the most acute phase of disease (at admission to inpatient treatment). Furthermore, the size of changes during and after treatment and weight rehabilitation in patients with AN compared to natural fluctuations of microbiome composition in healthy adolescents during normal development will be assessed. Again, mixed-effects models repeated measures analyses with an emphasis on descriptive reporting of confidence intervals of effect sizes will be performed.

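### Healthy controls entered about 18 months after the first patients, so the patient–control contrasts are partly confounded with calendar period, and the article names no check for it

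*Protocol article*

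**What the plan says.** The Trial status section gives the dates. For patients: "Recruitment of patients began in January 2020 with protocol version 4.3.2". For controls: "HC entered the trial at the end of June 2021 following postponing due to the COVID-19 pandemic". For the close: "Recruitment of both patients and HC is still open and will approximately be completed end of June 2022".

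Trial design {8} sets the control group: "For the 30 HC, only the measurement time points TA and T6 apply, and these participants will not receive any intervention". Recruitment {15} gives the matching: "Age- and sex-matched HC will be recruited via advertisements and flyers in schools in Aachen". Date of entry is not a matching factor.

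Objectives {7} places the control comparison inside the main objective, next to the placebo comparison: "in comparison to longitudinal changes in gut microbiome composition in healthy adolescents". The same section expects it to inform the disease mechanism and the degree of normalisation reached.

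Statistical methods {20a} plans two contrasts between patients of both arms and controls: microbiome composition and diversity at admission, and the size of change over treatment against natural fluctuation in healthy adolescents. Both use mixed-effects repeated measures models, with weight on descriptive confidence intervals. No covariate is listed for these contrasts. The sensitivity analyses in {20c} concern adherence and missing data.

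**The concern.** A contrast between patients and controls can be read as a disease effect only if the groups do not differ in other ways that move the outcome. Here they differ in when they were observed. Patients were sampled from the start of 2020, controls only from mid-2021, and the article itself attributes the gap to the pandemic. Diet, activity, infections and mood may have differed between these periods for reasons unrelated to anorexia nervosa. Outcomes {12} extends the comparison to questionnaires, step counts and serum markers, so the issue is not confined to the microbiome. Frozen stool and serum from the earliest patients may also have been stored up to about 18 months longer than the earliest control samples.

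At stake is a period difference reported as a feature of the illness, or as incomplete normalisation after treatment.

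**Working it through.** The article states no sample size or precision for the control comparison. Its only such figures (26 per group, 60 patients) concern PUFA versus placebo; they reproduce (a two-sample t-test gives 25.5, hence 26) and are not at issue.

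**Inputs from the article.** Patients from January 2020; controls from the end of June 2021; both to about the end of June 2022; 60 patients; 30 controls seen at admission-equivalent (TA) and month 6 (T6); patients also seen at month 12 (T12).

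**Assumptions.** Even accrual, 60/30 = 2 patients per month. A period shift, in SD units, between the months before and after control entry, unrelated to disease.

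**Overlap at admission.**
- Without controls: 18 of 30 months (17 of 29 if recruitment began at the end of January), or 59–60%.
- Patients before any control: 18/30 × 60 = 36 (35 with the later start).
- Patients concurrent with controls: 60 − 36 = 24.

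**Overlap at follow-up.**
- T6 visits after control entry: patients admitted from January 2021, 18 months × 2 = 36 of 60.
- T12 visits after control entry: patients admitted from July 2020, 24 months × 2 = 48 of 60.
- Controls' last T6 visits fall about the end of December 2022. T12 visits of patients admitted from January 2022 on (6 × 2 = 12) come later still, so 48 − 12 = 36 T12 visits lie inside the control window.
- A change from TA to T6 with both visits inside the window again needs admission from the end of June 2021: about 24 patients.

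**Bias of the unadjusted admission contrast** = share of patients before control entry × shift:

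| Assumed shift (SD) | Bias at 60% early | Actual error of a nominal 5% test |
|---|---|---|
| 0.2 | 0.6 × 0.2 = 0.12 | about 8% |
| 0.3 | 0.6 × 0.3 = 0.18 | about 12.5% |
| 0.5 | 0.6 × 0.5 = 0.30 | about 26% |

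If accrual was uneven and 40–80% of patients came early, a 0.3 SD shift gives 0.12–0.24 SD.

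**Can period and group be separated?** Yes. At admission there are three cells: early patients, late patients, late controls. A two-level period term without other covariates fits them exactly, so its group effect equals late patients minus controls.
- Variance, full sample: 1/60 + 1/30 = 0.050.
- Variance, concurrent: 1/24 + 1/30 = 0.075.
- Variance ratio 1.5; standard-error ratio √1.5 = 1.22.
- With 40% early: √[(1/36 + 1/30)/0.050] = 1.11. With 80% early: √[(1/12 + 1/30)/0.050] = 1.53.
- Difference detectable with 80% power: 0.63 SD for 60 versus 30, and 0.78 SD for 24 versus 30 (0.70–0.98 across 40–80% early).

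**The case against.** The strongest case for leaving the plan as it is runs as follows.

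- **Groups overlap.** A reader might infer that period effects fall entirely into the patient–control contrast. They do not: about 12 months are shared, and at follow-up more patient visits overlap with controls than at admission. This stands, and it is why the confounding is partial and can be checked.
- **The article is condensed.** A reader might infer that the trial has no analysis for this. That cannot be shown. The full protocol and any statistical analysis plan are not at hand, and covariates of an observational comparison are often fixed there. What can be said is that the article reports the delay, describes the affected contrasts, and does not connect the two. The version in force in January 2020 preceded the postponement; a later document may deal with it.
- **Nothing says the groups are treated as concurrent, or that samples are sequenced as they arrive.** Correct. The article says only that stool and serum are stored at −80°C, which is compatible with joint processing. A sequencing-run effect is a possibility to exclude, not a flaw in the text.
- **Several channels are measured.** Food protocols, activity bracelets, medication records and mood and anxiety scales exist in the trial. These help interpretation, but the control comparison does not commit to adjusting for them.
- **The consequence is limited.** PUFA and placebo are allocated concurrently in 1:1 blocks, so the co-primary comparisons are untouched. The control comparison is observational and reported descriptively. This stands and keeps the point minor. The comparison is nevertheless named in the main objective, and a confidence interval centred on a biased contrast misleads even without a test.

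**Conclusion.** The point holds as a minor improvement. Control entry lagged patient entry by about 18 months and overlaps it for about 12, matching ignores date, and the article names no period adjustment or concurrent-only check for contrasts that serve the main objective. Those contrasts are partly, not wholly, confounded with calendar period.

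The lag and the overlap come straight from the stated dates. The counts of 36 early and 24 concurrent patients rest on even accrual, which is doubtful in a pandemic. The bias of 0.12–0.30 SD rests in addition on an assumed shift of 0.2–0.5 SD, for which the documents give no figure and no direction. A true shift of zero would leave no bias.

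**What to change.** Keep the full-sample patient–control analysis and add one pre-specified sensitivity analysis for each contrast. Either include a calendar-period term based on the date of the sample or visit, or limit patient data to samples or visits from the end of June 2021 on. Select by visit date rather than admission date: restricting by admission would discard T6 and T12 samples taken while controls were being observed. For T12, state how visits after the last control visit are handled. Where the two analyses differ, report the contrast as non-concurrent.

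If samples are still unprocessed, distribute patient and control samples across sequencing and assay runs. If a later protocol version or an analysis plan already covers these points, a cross-reference is enough.

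The cost is one extra analysis and, where still possible, a plate layout. In the sensitivity analysis only, intervals for the admission contrast are about 22% wider under even accrual (11–53% if 40–80% of patients came early). A two-level period term also assumes that the shift is the same in patients and controls, because only patients were observed in the early period.

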## Data Availability

The anonymized final datasets that will be generated in this study will be available from the corresponding author on reasonable request after the publication of the trial results.

## Abbreviations

AE: Adverse event
AN: Anorexia nervosa
BDI-II: Beck Depression Inventory-II
BIS/BAS: Behavioral Inhibition System/Behavioral Activation System
BMBF: Federal Ministry for Education and Research
BMI: Body mass index
COVID-19: Coronavirus disease 2019
CRF: Case report form
CTC-A: Center for Translational & Clinical Research Aachen
DHA: Docosahexaenoic acid
DMC: Data Monitoring Committee
DTI: Diffusion tensor imaging
DSM-5: Diagnostic and Statistical Manual of Mental Disorders
EDE-Q: Eating Disorder Examination-Questionnaire
EDI-2: Eating Disorder Inventory-2
EHQ: Edinburgh Handedness Questionnaire
EPA: Eicosapentaenoic acid
HC: Healthy controls
HGF: Hierarchical Gaussian Filter
IGT: Iowa Gambling Task
ITT: Intention-to-treat principle
MAR: Missing at random
MNAR: Missing not at random
MINI Kid: Mini-International Neuropsychiatric Interview for Children and Adolescents
MRI: Magnetic resonance imaging
PRL: Probabilistic reversal learning
PUFA: Polyunsaturated fatty acids
SAE: Serious adverse event
SPM12: Statistical Parametric Mapping
SRS: Social Responsiveness Scale
STAI: State-Trait Anxiety Inventory
TAU: Treatment as usual
TBSS: Tract-Based Spatial Statistics
UPPS-P: Urgency, Premeditation, Perseverance, Sensation Seeking, and Positive Urgency Impulsive Behavior Scale
WAIS-IV: Wechsler Adult Intelligence Scale - 4th Edition
WISC-V: Wechsler Intelligence Scale for Children - 5th Edition
Y-BOCS: Yale-Brown Obsessive-Compulsive Scale
